#### Network Analyses

Baseline, mid-, post-, and follow-up data of current levels of symptoms and functioning will be modeled by network analysis to explore how networks differ by age, gender, diagnostic status, intervention condition, and assessment point in terms of centrality, closeness, betweenness, and clustering.

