Further efforts to optimize treatments and outcomes involve the modeling of mental disorders as a network of symptoms to identify central treatment targets [54]. According to the network perspective, a mental disorder is best understood as a complex system of dynamically interacting symptoms [55]. Central symptoms (eg, fear of humiliation) of such a network are supposed to spread quickly by activating other strongly interrelated symptoms, while bridging symptoms (eg, low self-esteem) may link clusters of symptoms. Both central and bridging symptoms may represent important intervention targets as they are supposed to be causally linked to other symptoms of an individual’s network [55-57]. To this point, studies of cross-sectional networks have demonstrated that dysfunctional cognitions function as central symptoms and influence multiple other social anxiety symptoms, especially behavioral components such as avoidance and safety behavior in adolescents [58,59]. Examining social anxiety as networks at symptom level over the course of the intervention could add to this knowledge by exploring whether participants’ network structures change from beginning to end of the intervention, in particular, by identifying relevant core and bridging symptoms as drivers of clinical change, by investigating differences in symptom networks between intervention and control group, and by studying the influence of possible moderators (eg, age, gender, and diagnostic status) on networks.

Overall, first studies suggest that online interventions have positive effects on adolescents with SAD; however, much uncertainty still exists about the efficacy of indicated prevention trials including adolescents with subclinical social anxiety. Moreover, previous research has focused mainly on the efficacy of interventions while neglecting both the mechanisms of change and the symptom-level network structure of SAD.

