The primary objective of this study is to examine the efficacy of an online intervention called SOPHIE for adolescents with subclinical social anxiety or SAD compared to a care-as-usual (CAU) control group. Thereby, the name SOPHIE is derived from the German term “SOziale PHobIE” (social phobia). It is hypothesized that SOPHIE will be superior to CAU in reducing social anxiety symptoms post assessment and that the intervention effect will be maintained until follow-up assessment 3 months after intervention completion. Furthermore, it is hypothesized that SOPHIE will also have beneficial effects on secondary outcomes, such as depressive as well as general anxiety symptoms, level of functioning, self-esteem, and quality of life at post assessment and follow-up. It is further hypothesized that intervention effects will be moderated by therapeutic alliance, adherence, treatment motivation, and treatment expectation of the online intervention. Moreover, by measuring social anxiety symptoms in their natural context longitudinally, we will examine if intervention effects translate into everyday life and if the postulated maintaining factors of SAD function as mediators of change. Additionally, we intend to model the network structure of social anxiety symptoms at each time point and observe differences in networks of adolescents (eg, regarding age, gender, and severity of social anxiety).

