### Procedures

Adolescents interested to take part in the study leave their email addresses on the study website [60]. They receive the participant study information by email and are asked to provide informed consent or assent (see Figure 1 for study flow). Participants younger than 14 years provide written assent, and their parent or guardian provides written consent. Participants 14 years or older provide consent on their own. Informed consents are accepted both on paper by mail and electronically as scans via email. Once the consent forms have been received, they are printed out and stored in analog form. Afterward, potential participants are screened for eligibility. Those with a score lower than 16 on the Social Phobia Inventory (SPIN) [61,62] are not included in the study but receive immediate access to the online intervention. The cutoff of 16 was chosen in reference to a previous study that showed good discrimination between healthy and subclinical adolescents [63]. Adolescents with a SPIN score of 16 or higher receive the remaining baseline questionnaires. Subsequently, they are interviewed by trained psychology graduate students via phone to ascertain whether they fulfill the diagnostic criteria for SAD or not. Those with a current diagnosis of SAD are assigned to the SAD group, while those with no current and no past SAD diagnosis are assigned to the subclinical social anxiety group. Training and weekly supervision of the graduate students are carried out by the first and last authors.

Participants are assigned to the intervention group or the control group by stratified block randomization to ensure that both groups are balanced regarding the diagnostic status: SAD or subclinical social anxiety. The randomization is carried out after all data collected by the diagnostic interview including diagnoses are entered into the electronic protocol form hosted on Qualtrics (Qualtrics XM) [64]. Randomization was set up before the start of the study by the first author (ie, number of groups, allocation ratio [1:1], and size of blocks). During the study, the allocation list was produced using an automated computer-generated random numbers table and was concealed from the investigators and the participants. After randomization, the intervention group receives immediate access to the online intervention.

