**Primary outcome**								
	Social anxiety	The *S**ocial Phobia Inventory* (SPIN) is a self-report questionnaire assessing 3 dimensions of social anxiety: fear, avoidance, and physiological symptoms. In 17 items, adolescents rate the frequency of each symptom on a 5-point Likert scale from *not at all* (0) to *extremely* (4) ([61], German version by [62]). The SPIN is a reliable self-report measure with good psychometric properties in adolescents [70,71]. Cut-off for subclinical social anxiety symptoms is set at 16 [63].	✓		✓		✓	✓

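### Comparing networks across assessment points mixes change with the SPIN entry cut-off: if SPIN items are nodes, overall connectivity is expected to rise after baseline even with no effect

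*Protocol article*

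**What the plan says.** **Entry.** Under Procedures, "Those with a score lower than 16 on the Social Phobia Inventory (SPIN) [61,62] are not included in the study". The next step is that "Adolescents with a SPIN score of 16 or higher receive the remaining baseline questionnaires". The word *remaining* shows that the SPIN used for screening is also the baseline SPIN.

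**Scale.** Table 1 describes the SPIN: "In 17 items, adolescents rate the frequency of each symptom on a 5-point Likert scale". It is given again at week 4, week 8 and follow-up, where no cut-off applies.

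**Networks.** The Introduction states that "we intend to model the network structure of social anxiety symptoms at each time point". The Network Analyses section says that "Baseline, mid-, post-, and follow-up data of current levels of symptoms and functioning will be modeled by network analysis", and the aim is "to explore how networks differ by age, gender, diagnostic status, intervention condition, and assessment point in terms of centrality, closeness, betweenness, and clustering". Assessment point and intervention condition are both in that list.

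**Intended reading.** The Introduction describes the interest as "exploring whether participants’ network structures change from beginning to end of the intervention", together with finding core and bridging symptoms that drive clinical change. It also mentions network differences between the intervention and control groups.

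**The concern.** Selecting people on a sum score shrinks the variance of that sum, and with it the associations among the items that make it up. Only the baseline data are cut this way. After entry, scores can move below 16 again, so spread and item associations recover. A baseline network and a later network can therefore differ although neither the network nor anyone's treatment has changed anything.

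At stake is one interpretation. A network that looks more tightly connected at week 8 than at baseline could be reported as change over the intervention when part or all of it comes from the entry rule. The same rise is expected in CAU. The primary and secondary outcome analyses are not touched.

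**Working it through.** **Inputs from the protocol.** Cut-off SPIN 16 or more on the baseline administration (Procedures); 17 items scored 0 to 4 (Table 1); correlation between measurements 0.4 and N = 56 + 166 = 222 (Sample Size); 1:1 allocation (Procedures), so 222/2 = 111 per arm.

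**Assumptions.** SPIN items are nodes. One factor underlies them, with unselected mean inter-item correlation ρ of about 0.33. The share p scoring below 16 is not given and is varied. A retest correlation of 0.7 is tried as an alternative.

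**1. The plan's own figure.** None is stated for the network analysis. The correlation of 0.4 is the one behind the sample size: with λ = N·m·f²/(1 − r), f = d/2 and m = 4,
- SAD: 56 × 4 × 0.175²/0.6 = 11.43, power 0.810
- subclinical: 166 × 4 × 0.10²/0.6 = 11.07, power 0.803

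Both stated sizes are reproduced.

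**2. Hand calculation.** For K similar items with unit variance, the item mean has variance g = [1 + (K − 1)ρ]/K = (1 + 16 × 0.33)/17 = 0.369. Removing the lowest share p of a roughly normal sum leaves the fraction k = 1 + a·h − h² of its variance, where a = Φ⁻¹(p) and h = φ(a)/(1 − p). Every item variance and covariance then loses D = g(1 − k). At a later visit with retest correlation R the loss is only R²D. So

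r(baseline) = (ρ − D)/(1 − D), and r(later) = (ρ − R²D)/(1 − R²D).

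- p = 15%: a = −1.036, h = 0.274, 1 − k = 0.360, D = 0.133. Baseline (0.33 − 0.133)/0.867 = 0.227; later, with R²D = 0.16 × 0.133 = 0.021, 0.309/0.979 = 0.315. Rise about 0.09.
- p = 3%: a = −1.881, h = 0.070, 1 − k = 0.137, D = 0.051. Baseline 0.294; later, with R²D = 0.008, 0.325. Rise about 0.03.

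**3. Simulation with ordinal items, no effect, identical network at both times, R = 0.4.** Mean inter-item correlation, baseline to later:

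| Screened out | Baseline | Later | Rise |
|---|---|---|---|
| 2% | 0.301 | 0.322 | 0.021 |
| 4.5% | 0.283 | 0.322 | 0.039 |
| 10% | 0.256 | 0.318 | 0.062 |
| 18% | 0.219 | 0.311 | 0.092 |

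A second simulation with other assumed loadings and thresholds gave 0.29 to 0.32 (3%), 0.27 to 0.32 (7%) and 0.24 to 0.31 (15%, about 0.08). With retest 0.7 and 18% screened out, the rise is 0.220 to 0.280. With nodes from a different scale on the same factor (18%, retest 0.4), it is 0.247 to 0.315, so the effect is smaller but does not vanish.

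**4. What a trial of n = 222 would show under the null.**
- Sum of partial correlations: rises in 99%, 94% and 80% of trials with 18%, 10% and 4.5% screened out.
- Absolute strength, closeness and clustering, unregularised networks: rise in 57–69% of trials over the same range.
- Lasso-regularised networks (3–15% screened out): strength rises in 85–99%, closeness in 69–94%, clustering in 74–97%.
- Betweenness, unregularised: rises in 43–46% (1.5–16% screened out), so no upward shift.
- Order of nodes: large-sample rank correlation of node strength between baseline and later at least 0.99.

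**5. Between-arm contrast.** The mean SOPHIE-minus-CAU difference in change of the summed partial correlations was −0.016, −0.009 and 0.001 (18%, 10%, 4.5% screened out), against uncontrolled rises of 0.48, 0.29 and 0.16.

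**The case against.** **Nodes are inferred.** The Network Analyses section names no instrument, and Table 1 also lists a second social anxiety scale, anxiety, depression and functioning measures. This stands: only SPIN items are cut on their own sum, and other nodes are affected indirectly and less.

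**Listed metrics.** The clearest shift is in mean correlation and summed partial correlations, neither of which is listed. This stands in part. Unregularised closeness and clustering are noisy at n = 222 and betweenness does not rise, so it would be wrong to say that every listed metric inherits the shift. With regularised networks, however, strength, closeness and clustering rise in most null trials.

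**False drivers.** A reader might infer that the cut-off would make the trial name the wrong central or bridging symptoms. The calculations do not show that. The cut-off lowers edges roughly evenly and leaves the node order in place, and a one-factor model has no symptom clusters and so says nothing about bridging.

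**No test is planned.** An illustrative within-person permutation test on mean correlation at the 5% level rejects in 93% of null trials with 24% screened out and in 18% with 3%. A reader might take these as the plan's false-positive rates. They are not: the plan states an exploratory aim and no test.

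**The unbiased contrast is already listed.** True, since intervention condition is among the comparison factors. That does not stop the assessment-point comparison, listed beside it, from being read as change.

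**Conclusion.** The point holds in limited form. If SPIN items are nodes, comparing the baseline network with later ones confounds change with the entry cut-off, and the expected direction under no change is a rise in overall connectivity. The expected rise in mean inter-item correlation is about 0.03 with 3% screened out and about 0.08 with 15%, at a retest correlation of 0.4. It is smaller with higher retest correlation and negligible if almost nobody scores below 16. These sizes rest on assumed loadings, thresholds and a one-factor structure.

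The bias concerns the level of connectivity: strength, and on average closeness and clustering, more visibly in regularised networks. It does not reach the SOPHIE-versus-CAU comparison at the same visit, because both arms passed the same cut-off. Since the analysis is exploratory, the importance is minor to moderate.

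**What to change.** In the Network Analyses section, base any statement about network change due to the intervention on the SOPHIE-versus-CAU difference at post and at follow-up, or on the between-arm difference in change from baseline. Report baseline-versus-later differences, within an arm or pooled, as descriptive only, and state that the SPIN cut-off of 16 lowers baseline connectivity.

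This takes a sentence or two and no new data. The cost is precision: each network rests on about 111 participants instead of 222, and the within-group description from beginning to end loses its standing as evidence of change.

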#### Sample Size

The sample size of 222 was determined in 2 a priori power analyses for the primary research question using G*Power [106] based on an intention-to-treat approach to account for possible dropouts and repeated measures ANOVA. In the SAD group, we expected a small to moderate effect size (Cohen *d*=0.35) [18,107], and for the group with subclinical anxiety, a small effect size (Cohen *d*=0.20) [38,108-110]. For both groups, we assumed an α level of 5%, power of 80%, and a correlation between measurements of *r*=0.4. Consequently, the SAD group should consist of 56 participants, and the subclinical social anxiety group of 166 participants.

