Meta-analyses have generally supported the efficacy of online interventions in adolescents [17]. These online interventions primarily targeted anxiety and depressive symptoms based on cognitive behavioral therapy (CBT). They have been demonstrated to be superior to passive control conditions (eg, waitlist) and equally efficacious to active control conditions (eg, face-to-face CBT) [18]. Notably, face-to-face interventions targeting several anxiety disorders simultaneously are less efficacious in patients with SAD than other anxiety disorders [19-22]. This emphasizes the need for interventions specifically targeting symptoms of social anxiety such as those proposed in the Clark and Wells or Heimberg model [22,23]. Face-to-face trials imply that the Cognitive Model of social anxiety by Clark and Wells [24] also applies to adolescent samples [25-27]. Online interventions targeting social anxiety in adolescents showed large effects compared to passive (ie, waitlist [28,29]) and active control conditions (ie, online support [30]) but, unlike the face-to-face trials, was equally efficacious compared to a generic CBT program for anxiety [29]. These results are promising but need to be interpreted cautiously as some studies primarily focused on a small sample size with older adolescents with speech anxiety [28] or reported high dropout rates in the study and low adherence rates to the online intervention [29]. Poor engagement with online interventions is a known issue [17]. Human support in the form of guidance (eg, sending summaries and reminders and answering questions) can enhance adherence to and effects of online interventions in adult samples [31,32]. So far, there is no conclusive evidence about adolescents; nevertheless, initial studies suggest that guidance is generally accepted and beneficial for adherence and efficacy [33-36].

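### The 80% power stated for each stratum does not follow from the stated effect sizes: 56 and 166 appear to rest on an interaction effect about 2.3 times larger, with no allowance for dropout

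*Protocol article*

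**What the plan says.** The Sample Size section of the protocol article describes two a priori G*Power calculations, one per diagnostic stratum.

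- SAD stratum: "we expected a small to moderate effect size (Cohen *d*=0.35").
- Subclinical stratum: "a small effect size (Cohen *d*=0.20").
- Common inputs: "For both groups, we assumed an α level of 5%, power of 80%, and a correlation between measurements of *r*=0.4".
- Result: "Consequently, the SAD group should consist of 56 participants, and the subclinical social anxiety group of 166 participants".
- Method and dropout, in one phrase: "based on an intention-to-treat approach to account for possible dropouts and repeated measures ANOVA".

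The section does not state the f value entered, which repeated measures ANOVA effect was tested, or how many measurements were assumed. Study Design gives four occasions (baseline, week 4, week 8 and the 3-month follow-up), and Procedures gives 1:1 allocation. The Introduction places the primary hypothesis at post assessment, with maintenance to follow-up. Main Analyses specifies one mixed model over four times for both strata together, with baseline SPIN as covariate, and singles out no visit.

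**The concern.** A total of 56 means 28 per arm. A simple two-group comparison at d = 0.35 needs far more than that for 80% power, so the stated number can be right only if the repeated measures supply a very large gain. At r = 0.4 they do not. The likely cause is the effect-size conversion: f = d/2 is correct for a constant difference between two group means, but not for a group-by-time interaction.

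The article presents each stratum as a separately powered comparison. The Discussion expects the trial to show whether one programme can serve both as indicated prevention and as therapy, and that depends on the stratum results. If the real power is well below 80%, a non-significant result in a stratum is a likely outcome even when the expected effect is present, and the printed figure invites a reader to take it as a negative finding.

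**Working it through.** **Inputs.** d = 0.35 and 0.20, α = 0.05 (taken as two-sided), r = 0.4 and N = 56 and 166 (Sample Size); m = 4 measurements (Study Design); 1:1 allocation (Procedures).

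**1. Reproduce the plan's figures.** In G*Power's within-between interaction test, λ = f²·N·m/(1 − r), with (m − 1) and (N − 2)(m − 1) degrees of freedom. Put f = d/2:

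- SAD: f = 0.175; λ = 0.030625 × 56 × 4 / 0.6 = 11.43; df 3 and 162; power 0.810. N = 54 gives 0.794.
- Subclinical: f = 0.10; λ = 0.01 × 166 × 4 / 0.6 = 11.07; df 3 and 492; power 0.803. N = 164 gives 0.798.

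So 56 and 166 are exactly the smallest even totals that reach 80%. The other group-comparison settings tried do not fit: m = 2 gives 80/238, m = 3 gives 66/196, the between-group test with f = d/2 gives 144/434, and f = d gives 16/44. A one-group time effect gives 55/165 but compares no groups.

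**2. The f that the stated d implies.** In this test, f is the standard deviation of the group-by-time interaction effects over the cells. Take arms equal at baseline and differing by d at the three later visits: (0, d, d, d). The mean is 0.75d and the variance over visits is (0.75² + 3 × 0.25²)d²/4 = 0.1875d². Each arm carries half the difference, so f = √(0.1875/4)·d = 0.217d. Entering 0.5d overstates f by 0.5/0.2165 = 2.3. The stated Ns therefore fit a difference of about 0.81 (SAD) or 0.46 (subclinical).

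With the implied f:

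- SAD: f = 0.0758, λ = 2.14, power 20.0%.
- Subclinical: f = 0.0433, λ = 2.08, power 19.7%.

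**3. More favourable contrasts.** For the baseline-adjusted mean of k post-baseline visits, the variance factor is v = (1 + (k − 1)r)/k − r², and SE = √(4v/N) in SD units. Power uses the noncentral t with N − 3 degrees of freedom. The pooled d is (56 × 0.35 + 166 × 0.20)/222 = 52.8/222 = 0.238.

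| Contrast (full d at each visit averaged) | v | SAD | Subclinical | Pooled, N = 222 |
|---|---|---|---|---|
| Week 8 | 0.84 | 28.9% | 28.7% | 48.6% |
| Mean of week 8 and follow-up | 0.54 | 41.7% | 41.4% | 67.0% |
| Mean of weeks 4, 8 and follow-up | 0.44 | 49.1% | 48.8% | 75.8% |

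If only half of d is present at week 4, the pooled three-visit figure falls to about 60%. If r were 0.7 instead of 0.4, week-8 power per stratum would be about 44% (SAD) and 43% (subclinical).

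The smallest d with 80% power at week 8 is about 0.70 (SAD), 0.40 (subclinical) and 0.35 (pooled).

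**4. Dropout.** The calculation in step 1 uses all 56 and all 166, so nothing was added for loss. The article gives no rate. Assuming 10%, 20% and 30% loss, with lost participants contributing nothing:

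- The plan's own calculation falls to about 76%, 70% and 63%.
- The week-8 contrast falls to about 26%, 24% and 21% per stratum, and 45%, 41% and 36% pooled.

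The Introduction itself notes that an earlier online study in this field "reported high dropout rates in the study and low adherence rates to the online intervention".

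**The case against.** Several points on the other side are fair.

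- **The conversion is inferred.** No f and no ANOVA option are printed. Two exact matches make the inference strong, but it should be worded as what appears to have been done. The shortfall itself does not depend on it, because steps 2 and 3 use only the stated d, r and N.
- **The meaning of d is not defined.** The figures read it as a standardized between-group difference. That is the usual meaning and suits the hypothesis of superiority over CAU, but the article does not spell it out.
- **A reader might infer that true power is 20–29% per stratum, full stop.** That range covers only the interaction test and week 8. Averaging visits raises it to 42% or 49%.
- **A reader might infer that the trial as a whole is hopelessly underpowered.** The planned mixed model uses both strata, and the pooled three-visit mean reaches about 76% if the full effect is present at every post-baseline visit. This is close to 80%, but it is the best case tried and is not the per-stratum claim that the article makes.
- **A reader might take week 8 as the designated primary contrast.** The hypothesis names post assessment, but Main Analyses designates no visit and the Abstract compares groups at each time point. Week 8 is one candidate.
- **The dropout figures are a worst case for the longitudinal analysis.** The mixed model and the planned multiple imputation keep partial data, and the rates are assumptions.

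None of this restores 80% in either stratum.

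**Conclusion.** The point holds. At the stated effect sizes, r = 0.4 and no dropout, power per stratum is about 20% to 49% depending on the contrast. No contrast tried reaches the stated 80%. Pooled power is about 49% at week 8 and up to about 76% for the three-visit mean. The stated Ns fit a post-baseline difference about 2.3 times the one printed.

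The claim that intention-to-treat accounts for dropout is also wrong as written: it governs who is analysed and does not replace lost information.

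These results assume that d is a standardized between-group difference, a two-sided 5% test and equal correlation of 0.4 between all visits. The pooled figures also assume a weighted mean effect of 0.24. The documents do not support the stronger conclusion that the trial cannot answer its question or must recruit more. What fails is the power statement, and with it any reading of a null stratum result as evidence of no effect.

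**What to change.** Keep N = 222 and rewrite the Sample Size paragraph.

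1. Name the contrast that the primary test uses, for example the post-assessment comparison in the Introduction's hypothesis.
2. Replace the 80% statement with power computed for that contrast, per stratum and pooled, and print the effect measure, the test and the number of measurements used. If week 8 is chosen: about 29% per stratum at d = 0.35 and 0.20, about 49% pooled at d = 0.24, and 80% power only for d of about 0.70 (SAD), 0.40 (subclinical) and 0.35 (pooled).
3. Delete the claim that intention-to-treat accounts for dropout, and give power over an assumed attrition range, labelled as an assumption.
4. State that the stratum-specific comparisons do not have 80% power at the stated effects, so a null result there is not evidence of no effect.

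The cost is a reworded paragraph, a decision on the primary contrast and a less favourable power figure. No extra participants are needed.

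### The 80% power claimed in each diagnostic stratum is not reached at the stated Cohen d: 56 and 166 come out of the calculation only if the arms differ by at least twice that d

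*Protocol article*

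**What the plan says.** The Sample Size section describes two a priori calculations, one per diagnostic stratum, made "using G*Power [106] based on an intention-to-treat approach to account for possible dropouts and repeated measures ANOVA". The effect sizes are Cohen d = 0.35 for SAD and d = 0.20 for subclinical social anxiety. The common inputs are given as "For both groups, we assumed an α level of 5%, power of 80%, and a correlation between measurements of *r*=0.4". The result is "Consequently, the SAD group should consist of 56 participants, and the subclinical social anxiety group of 166 participants", 222 in total.

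The section does not say which ANOVA effect was tested (between, within or interaction), or how d became the f that a repeated measures ANOVA calculation needs.

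The hypothesis to be powered is in the Introduction: "It is hypothesized that SOPHIE will be superior to CAU in reducing social anxiety symptoms post assessment". Study Design gives two arms and four assessments, and Procedures gives 1:1 allocation. Main Analyses specifies a linear mixed model over all participants, with time-by-condition terms and baseline SPIN as covariate.

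**The concern.** The conversion f = d/2 is right for two means compared at one time. In a time-by-condition interaction, f measures how much the arm difference varies over visits. Randomisation makes the expected baseline difference zero, and an effect of size d at later visits gives an interaction f well below d/2. If f = d/2 was entered for the interaction, the calculation assumed a much larger treatment effect than the d in the text.

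What is at stake is the one design property that the article claims for each stratum. The Discussion presents the trial as informing whether one programme can serve as both indicated prevention and therapy, so stratum results matter separately. A reader who trusts 80% power would give a non-significant stratum result more weight than it can carry.

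**Working it through.** **Inputs.** Sample Size: d = 0.35 and 0.20, alpha 5%, power 80%, r = 0.4. Study Design: k = 2 arms, m = 4 visits. Procedures: 1:1 allocation. Complete data, equal SDs and a common correlation are assumed throughout.

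**1. Reproducing the plan's figures.** Noncentrality lambda = f² × N × m / (1 − r), with df 3 and 3(N − 2), and f = d/2.
- SAD: f = 0.175; lambda = 0.030625 × 56 × 4 / 0.6 = 11.43; power 0.810. N = 54 gives 0.794.
- Subclinical: f = 0.10; lambda = 0.01 × 166 × 4 / 0.6 = 11.07; power 0.803. N = 164 gives 0.798.

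So 56 and 166 are the smallest even N that reach 80%. This is the within-between interaction. With two groups, the within-factor (time) test has the same lambda and df and gives the same numbers, but it does not compare the arms. Other variants do not match (SAD / subclinical): interaction with 2 visits 80 / 238, with 3 visits 66 / 196; between-arm factor 144 / 434; interaction with f = d 16 / 44; two-sample comparison at one visit 258 / 786.

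**2. The interaction f that the stated d can produce.** Let δ_t be the arm difference at visit t in SD units. Then f² is the mean over visits of ((δ_t − mean δ)/2)², so f is half the SD of the δ_t over visits. Values between 0 and d have an SD of at most d/2, so f is at most d/4. The profile (0, 0, d, d) reaches this ceiling. To get f = d/2, the later arm differences must reach 2d for that shape: 0.70 (SAD) and 0.40 (subclinical). For (0, x, x, x) they must be 0.81 and 0.46; for (0, x/2, x, x), 0.84 and 0.48.

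**3. Power of the 3-df time-by-condition test at the stated d.** lambda = (N/4) × Σ(δ_t − mean δ)² / 0.6.

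| Arm differences at the 4 visits | f, SAD / subclinical | Power, SAD / subclinical |
|---|---|---|
| 0, 0, d, d | 0.0875 / 0.0500 | 0.257 / 0.253 |
| 0, d, d, d | 0.0758 / 0.0433 | 0.200 / 0.197 |
| 0, d/2, d, d | 0.0726 / 0.0415 | 0.186 / 0.183 |
| 0, d/2, d, d/2 | 0.0619 / 0.0354 | 0.145 / 0.143 |

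For (0, d, d, d), lambda is 0.1875 × 4 = 0.75 of the (0, 0, d, d) value and 0.1875 of the value in step 1.

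**4. Single between-arm contrasts at the stated d.** Noncentrality = d × √N / (2s), where s is the residual SD.
- Post, unadjusted (s = 1): 1.31 / 1.29; power 0.25 / 0.25.
- Post, baseline-adjusted (s² = 1 − 0.4² = 0.84): 1.43 / 1.41; power 0.29 / 0.29.
- Mean of the three later visits, baseline-adjusted, constant d (s² = (1 + 2 × 0.4)/3 − 0.16 = 0.44): 1.97 / 1.94; power 0.49 / 0.49.

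**5. Pooled strata.** Weighted d = (56 × 0.35 + 166 × 0.20)/222 = 0.238, N = 222. Baseline-adjusted post contrast: power 0.49. Baseline-adjusted three-visit mean: 0.238 × √222 / (2 × √0.44) = 2.67; power 0.76.

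**6. Detectable d with 80% power per stratum.** Baseline-adjusted post contrast: 0.70 / 0.40. 3-df test with profile (0, d, d, d): 0.80 / 0.46.

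**The case against.** **The diagnosis is inferred.** The article never writes f = d/2 or names the interaction, and the time test gives the same N. A reader might infer that the interaction with f = d/2 is the only route to 56 and 166; the numbers do not single it out. This objection stands against any claim to know what was entered. It does not rescue the power, because a time test says nothing about SOPHIE versus CAU.

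**d may not be a between-arm difference.** The works cited for d cannot be seen here. The Introduction describes one of the two sources for the SAD value through comparisons with controls ("They have been demonstrated to be superior to passive control conditions (eg, waitlist) and equally efficacious to active control conditions"); for the subclinical value the definition of d cannot be checked. The between-arm reading therefore remains an assumption. It fits the stated hypothesis, and the article offers no other definition.

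**The primary model pools the strata and uses all visits.** This is the strongest point. The pooled three-visit mean reaches about 76% at r = 0.4 and about 82% at r = 0.6. Within a stratum, r = 0.8 would give 57% for the adjusted post contrast and about 77% for the three-visit mean. But the three-visit figures need a constant d from week 4 onward, the higher ones need an r that the plan does not use, and the article attaches 80% to each stratum separately.

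**The misreading is hypothetical.** Nothing in the article says that a null stratum result will be taken as no effect. That is a risk to guard against, not a stated intention.

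**Conclusion.** The point holds. At the stated d and r, no between-arm test examined gives 80% power within a stratum. The ceiling is about 26% for the 3-df interaction when arm differences lie between 0 and d, 29% for the post contrast, and about 49% for the three-visit mean. Dropout would lower all of these.

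The conclusion rests on reading d as the between-arm standardised difference, on complete data and on r = 0.4. The d/4 limit needs only that arm differences stay between 0 and d.

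A reader might infer that the trial's true power is one figure near 25%. The documents do not support that: the answer depends on the contrast, the time course and whether strata are pooled, and runs from about 14% to 49% per stratum and up to about 76% pooled. Nor is there a slip in arithmetic, since the sums reproduce. The fault lies in the effect size that the calculation implies.

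**What to change.** Keep the sample size. In the Sample Size section:

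1. Name the ANOVA effect that was tested and the d-to-f conversion that was used, so that the record of how 56 and 166 arose is complete.
2. Replace the claim of 80% power per stratum with wording such as: *Taking d as the between-arm standardised difference, with complete data and r = 0.4, power per stratum at d = 0.35 (N = 56) and d = 0.20 (N = 166) is about 14-26% for the 3-df time-by-condition test (20% if the difference is d at all three later visits), 25% for the post contrast unadjusted and 29% baseline-adjusted, and at most about 49% for the baseline-adjusted mean of the three later visits with constant d. Pooled over 222 participants (weighted d about 0.24), baseline-adjusted power is about 49% at post and about 76% for the three-visit mean. Per stratum, 80% power is reached at d of about 0.70 and 0.40 (baseline-adjusted post contrast) or 0.80 and 0.46 (3-df test with equal differences at the three later visits).*
3. Add that a non-significant result within a stratum will be reported as its estimate with confidence interval and not as absence of effect.

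The cost is one reworded paragraph and a much less favourable power statement. No extra participants are needed.
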